## Study period overview

All patients needing platelet transfusion will be screened for study eligibility (Fig. 1). Upon enrolment, recruited patients will be randomised to one of the two treatment arms (i.e. platelet transfusion with vWF or placebo) with consecutive ICU follow-up for 2 days (Table 1). It will not be allowed to administer another dose of Wilate®/placebo for the study period of 48 h after the first dose was given.

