It is recommended to administer 20–50 IE of Wilate® per kg/BW in vWF patients with acute bleeding. The dosage of Wilate® in this trial will be 2000 IU of vWF and 2000 IU factor VIII each in combination with one or two platelet concentrates. The medication (Wilate® or placebo and platelet concentrates) will be administered intravenously, because this is the only possible route of administration of Wilate® and platelets. The objective of this treatment is to stop the haemorrhage by administering the intervention drug once. Due to the long half-time of the study drug, a single administration will be sufficient for the 48-h observation period, also in cases where further thrombocyte transfusions are needed.

To make sure the study drug will be distributed within the body, a minimum waiting period of 10 min should be met whenever possible and depending on the clinical picture before platelet concentrate transfusion (usually this is the case as platelet concentrates have to be ordered in most situations). A waiting period of 20–30 min would be ideal. Thereafter, the clinical situation should be reassessed and the decision to transfuse a second platelet concentrate be taken after careful consideration.

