## Randomisation

The trial staff will have permanent access to the electronic case report form where patients are screened and randomised to one of the study arms. Randomisation will be performed via the electronic case report form using REDCap® after checking the eligibility of the patient. A unique patient identification code will be assigned to every screened patient without possible inference to patient identity.

To achieve a balance in the participants in the two trial groups for a small sample size, we plan to perform the so-called block randomisation. The same principle will be performed for the randomisation of the study pack’s serial number. There will be no special criteria for discontinuing or modifying allocated interventions.

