## Safety

During the entire duration of the study, all adverse events (AE) and all serious adverse events (SAEs) are collected, fully investigated and documented in source documents and case report forms (CRF). Study duration encompassed the time from when the participant signs the informed consent until the last protocol-specific procedure has been completed, including a safety follow-up period.

Post-trial management will not differ from management during the study period and patients will be followed as described in the ‘Study period overview’ section.

An individual subject will be excluded from the study in case of the following:Withdrawal of consent by the independent physician or next of kinAn adverse event that in the opinion of the sponsor contraindicates further measuring (emergency setting)

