## Patient withdrawal

Patients withdrawn (excluding ex-post-study withdrawal) from the study and subjects who could not be followed over the intended period and for all designated points of assessments, regardless of reason will be included in the intention-to-treat analysis. Unless consent for follow-up is withdrawn, subjects discontinued before closeout will be followed for the full study period, and all laboratory and clinical evaluations will occur as defined in the protocol. We can guarantee that the measurements will by no means delay therapy.

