#### Primary analysis

Evaluation of the effect of Wilate® compared to placebo on the outcome number of blood products (TC, EC, FFP) administered using negative binomial regression. The following covariates will be included: blood loss, number of blood products transfused within 12 h before administration of the study drug, anticoagulants 7 days before, the site of bleeding and the level of thrombocytes at baseline.

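### The adverse-event ground for excluding a patient from the study conflicts with the full follow-up and analyse-everyone rules, and in a single-dose trial it can only cost outcome data

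*Protocol article*

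**What the plan says.** The Safety section opens its list with "An individual subject will be excluded from the study in case of the following". One item is withdrawal of consent by the independent physician or next of kin. The other is an "adverse event that in the opinion of the sponsor contraindicates further measuring", with a bracketed reference to the emergency setting.

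The Patient withdrawal section says that "subjects discontinued before closeout will be followed for the full study period, and all laboratory and clinical evaluations will occur as defined in the protocol". Its one stated exception is withdrawal of consent for follow-up. On the intention-to-treat analysis, it adds that "subjects who could not be followed over the intended period and for all designated points of assessments, regardless of reason will be included". Under Datasets to be analysed, the only ground for not analysing an included patient is retrospective withdrawal of informed consent.

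The drug is given once. The study medication section says that "a single administration will be sufficient for the 48-h observation period", and the Study period overview says of the 48-hour period: "It will not be allowed to administer another dose". The Blinding section adds that a patient's arm is unblinded in case of a serious adverse event.

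**The concern.** In a trial with continued dosing, an adverse-event rule of this kind would normally protect the patient by stopping treatment. Here the single dose has already been given, so the rule can end only observation.

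Two features make that loss undesirable. First, the trigger is an adverse event judged by the sponsor, without a defined criterion. Loss is then tied to the patient's course and is not random. Second, unblinding after a serious adverse event can come before the decision, so the judgement may be made with the arm known. The product supports coagulation, and thromboembolic complications are a listed outcome. The patients most likely to fall under the rule are therefore those whose later course matters most for both efficacy and safety.

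**Working it through.** The plan gives no number for adverse-event exclusions. Under Handling of missing data and drop-outs it says only that dropouts and missing data should be few. The check is therefore mainly a comparison of the text.

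**1. Can the rules hold together?**

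| Rule | Section | Patient excluded for an adverse event |
|---|---|---|
| Excluded when the sponsor judges that further measuring is contraindicated | Safety | Leaves the study; measuring stops |
| Followed for the full period; only exception is withdrawn consent for follow-up | Patient withdrawal | Must still be followed, with all evaluations |
| Analysed; only exception is retrospective consent withdrawal | Datasets to be analysed | Must be in the analysis |

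The consent item in the Safety list fits the exception in Patient withdrawal. The adverse-event item fits no exception. Taken literally, the first and second rules cannot both be obeyed. If exclusion also means removal from the analysis, the third is broken too.

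**2. Which data could an adverse event make it wrong to collect?**

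- Table 3 takes red cell, plasma and platelet counts from Metavision, the patient data management system.
- One-year mortality comes from a governmental registry through the social security number, with personal contact for patients without a valid number.
- Thromboembolic events are entered in REDCap (Table 3) and, under Adverse events, registered until hospital discharge.
- The consent section names the study-specific blood specimens: the VerifyNow ADP test and the vWF:RCo test.

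Only the last group needs extra sampling for the study. The primary outcome does not.

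**3. What happens to the 48-hour count?** The primary analysis is of the "number of blood products (TC, EC, FFP) administered using negative binomial regression". The article does not say how a count that stops before 48 hours enters it. Three readings are open:

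- The count is completed from the clinical record, as Patient withdrawal implies. No bias.
- The partial count is kept. That patient's use is understated.
- The patient is dropped. This is a post-randomisation exclusion.

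Data handling and management allows data up to the point of withdrawal to be used, with none collected afterwards. It says so for a patient's own withdrawal, so it does not settle the adverse-event case.

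**4. Size under the partial-count reading.** Let f1 and f0 be the shares cut short in the Wilate and placebo arms, and s the share of the 48-hour count already observed, for patients of average need. The expected ratio of means becomes

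R_observed = R_true × [1 − f1(1 − s)] / [1 − f0(1 − s)].

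- If f1 = f0, the factor is 1 and the ratio is unchanged.
- If f0 = 0, the proportional shift is f1(1− s), which cannot exceed f1.
- With 60 patients per arm, one extra patient cut short in one arm gives f1 = 1/60, so at most 1/60 = 1.7%. The shift grows in proportion if that patient's need is above average.

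The plan states neither f1, f0 nor s, so no total can be given. For comparison, the trial is sized for a 50% reduction.

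**The case against.** The strongest reply is that the item means less than it says. If transfusion counts come from the routine record, no adverse event could contraindicate them. Measuring, next to the reference to the emergency setting, would then mean study blood sampling. The closing assurance in Patient withdrawal that measurements will not delay therapy points the same way. On that reading the primary count is never cut short. This is a fair reading, and it is the one the fix would write in. But the sentence speaks of exclusion from the study, not of a skipped sample, so the text does not secure it.

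A second reply is that rules for incomplete counts belong in the statistical analysis plan, which the Statistics section announces and which is not shown. That stands for the analysis, and the absence of such a rule here is not held against the article. It does not dispose of the conflict, because an analysis plan does not decide who continues to be observed.

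A third reply is that few patients will be affected. Nothing in the article contradicts this, and it limits the weight of the point.

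A reader might also see a contradiction with the Randomisation section: "There will be no special criteria for discontinuing or modifying allocated interventions". There is none. That sentence concerns interventions, and leaving the study after a single dose discontinues no intervention.

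**Conclusion.** The point holds as an internal conflict. The adverse-event item under Safety cannot be squared with Patient withdrawal or, if exclusion reaches the analysis, with the analysis population. It opens a discretionary route to informative loss that may be informed by the arm, with no gain in stopping study treatment. This rests on reading exclusion from the study literally. The arm-informed part also assumes that the result of an unblinding can reach whoever makes the decision; the Blinding section does not say who is told.

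Bias in the primary comparison is possible but not shown. It needs observation to stop before 48 hours, the count to be left incomplete or the patient dropped, and exclusions that differ by arm in number, timing or type of patient. It would be small if such cases are few or balanced.

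Two stronger readings should be resisted. A reader might infer that patients cut short are scored as low users of blood; no section says so, and completion from the record is equally open. A reader might also extend the point to deaths within 48 hours. That question would remain if the adverse-event item were removed, and its handling may be in the analysis plan.

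**What to change.** Reconcile the Safety list with Patient withdrawal and Datasets to be analysed. State that:

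- an adverse event may lead only to omission of the study-specific samples (VerifyNow and vWF), not to exclusion from the study;
- transfusions to 48 hours, thromboembolic events and mortality continue to be taken for that patient from the clinical record, the case report form and the registry;
- these data are analysed by intention to treat in the allocated arm;
- withdrawal of consent remains the only ground for ending data collection.

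The change concerns data collection only and leaves clinical care untouched. It costs a few sentences of protocol wording, with no added visits, staff or samples.

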### Serious adverse reactions

The occurrence of serious adverse events (SAEs) will be assessed during every shift based on the bedside visit and results of vital and laboratory parameters and will be recorded daily on the electronic case report form.

All changes in research activity and unanticipated problems will be reported to the competent Ethics Committee by the sponsor and the principal investigator. An SAE or a serious unexpected adverse drug reaction (SUSAR) must be reported within 7 days if fatal, otherwise within 15 days. The sponsor will provide an annual safety report.

### Relevant concomitant care needs

Since co-administration of Wilate ® to platelets until today is neither part of transfusion guidelines nor part of the indications of Wilate ® implementing platelets with placebo or platelets with Wilate ® will not require alteration to usual care pathways (including use of any medication) for emergency treatment for patients, and these will continue for both trial arms.

## Patient withdrawal

Patients withdrawn (excluding ex-post-study withdrawal) from the study and subjects who could not be followed over the intended period and for all designated points of assessments, regardless of reason will be included in the intention-to-treat analysis. Unless consent for follow-up is withdrawn, subjects discontinued before closeout will be followed for the full study period, and all laboratory and clinical evaluations will occur as defined in the protocol. We can guarantee that the measurements will by no means delay therapy.

## Statistics

Detailed methodology for summaries and statistical analyses of the data collected in this study will be documented in a statistical analysis plan, which will be finalised before database closure and will be under version control by the statistician responsible for the Will-Plate study.

### Hypothesis

Patients with clinical bleeding and an indication for platelet transfusion in the ICU setting have a significant lower number of further blood products (EC, TC, FFP) transfused within the first 48 h after treatment with Wilate® compared to transfusion alone.

### Determination of sample size

A total of 120 (each group 60) patients are needed to detect a 50% reduction of the number of blood products subsequently transfused within two days in patients with Wilate® compared to placebo. The sample size is calculated for a power of 80 % and a significance level of 5% for an estimate of the treatment effect evaluated with a negative binomial regression. To improve the precision of the treatment effect, the following covariates will be included: blood loss, number of blood products transfused within 12 h before administration of the study drug, anticoagulants administered 7 days before, the site of bleeding and the level of thrombocytes at baseline. The sample size calculation is based on a simulation applying resampling techniques on historical clinical data of 150 USB patients that meet the inclusion criteria.

### Planned analyses

#### Datasets to be analysed, analysis populations

All analyses are intention-to-treat analyses. All patients included in the trial will be analysed unless informed consent is withdrawn retrospectively. The description of the dataset is described elsewhere.

#### Primary analysis

Evaluation of the effect of Wilate® compared to placebo on the outcome number of blood products (TC, EC, FFP) administered using negative binomial regression. The following covariates will be included: blood loss, number of blood products transfused within 12 h before administration of the study drug, anticoagulants 7 days before, the site of bleeding and the level of thrombocytes at baseline.

#### Secondary analyses

##### Thrombocytes activity

The *T*-test evaluates the difference in the outcome between the two study groups. The outcome is defined as the difference in the platelet reaction units (PRU) measured with the VerifyNow® ADP test before and after the transfusion of TC.

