**Fig. 1 Fig1:**
[figure not shown]
Study flow chart

**Table 1 Tab1:** Study overview

***Visit***	***Screening***	***Treatment***	***Assessment***	***ICU follow-up***		***30-day and 1-year follow-up***^***b***^
*Time (hours, days, weeks)*	*− 1 h*	*0*	*30–60 min*	*1 day*	*2 days*	*12 months*
*Patient information and informed consent*	*x*^*a*^	*x*^*a*^	*x*^*a*^	*x*^*a*^	*x*^*a*^	
*Demographics*	*x*					
*Medical history*	*x*					
*In-/exclusion criteria*	*x*					
*Vital signs*	*x*		*x*	*x*	*x*	
*Platelet function analysis*	*x*		*x*			
*Laboratory tests*	*x*		*x*	*x*	*x*	
*Pregnancy test*	*x*					
*Randomisation*		*x*				
*Information related to bleeding*	*x*		*x*	*x*	*x*	
*Study medication*		*x*				
*Primary outcome variable*			*x*	*x*	*x*	
*Secondary outcome variables*			*x*	*x*	*x*	*x*
*Adverse events*			*x*	*x*	*x*	
*Mortality* *ICU* *Hospital* *30 days* *1 year*				*x*	*x*	*x*

^a^If not possible so far

^b^Assessment of ICU and hospital length of stay, ICU and hospital mortality, 30-day mortality, 1-year mortality, and estimated costs of blood transfusion products

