#### Laboratory parameters

Blood counts and global tests for coagulation, clinical chemistry biomarkers, vWF and FVIII levels and haemoglobin concentration will be analysed. Blood samples will be drawn during regular time points on the intensive care unit (e.g. 6 a.m.) except for the global platelet function analysis (VerifyNow®), which will be analysed right before the first study-specific platelet transfusion and 30–60 min after administration of the study drug and platelets.

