### Primary outcome measure

#### Number of transfusions

This is the number of blood products (fresh frozen plasma (FFP), RBCs, platelet concentrates) transfused within the first 48 h after study allocation in both groups (Tables 2 and 3).

**Table 2 Tab2:** Baseline data assessed upon study inclusion (data prior/upon admission to ICU) to be documented *before* administration of the study drug

	***Metavision®***	***RedCap®***
Informed consent or statement of an independent physician		X
Randomisation, assignment of the group		X
Demographics^a^	X	
Admission diagnosis		X
Past medical history		X
Relevant medication prior to bleeding (1 month)^b^		X
Type of admission (medical, surgical)		X
SAPS II	X	
SOFA score	X	
Type of surgery (if applicable)		X
Cause of bleeding		X
Reason for thrombocyte transfusion		X
Amount of blood loss prior to ICU admission	X	
Vital parameters^c^	X	
Lowest temperature measured^d^	X	
Lowest temperature measured		
Fluid balance^e^	X	
Full blood count and chemogram^f^	X	
Coagulation laboratory^g^	X	
Platelets function analysis (VerifyNow® ADP test) *before* administration of the study drug		X
Number of given RBCs	X	
Number of given FFPs	X	
Number of given platelet concentrates	X	
Amount of prothromblex	X	
Amount of tranexamic acid	X	
Amount of fibrinogen	X	
Name/amount of other given coagulation products^h^	X	
Transfusion-related side effects (AE, SAE)	X	
Thromboembolic events	X	

^a^Age, sex, BMI, height, social security number (identification log only)

^b^NOACs, antiplatelet agents and oral anticoagulation such as Marcumar® (phenprocoumon), Eliquis® (apixaban), Lixiana® (edoxaban), Xarelto® (rivaroxabam), Pradaxa® (dabigatran), Aspirin ® (ASS) and Plavix® (clopidogrel)

^c^Blood pressure, pulse, SpO_2_, ScvO_2_, SvO_2_ and respiratory rate

^d^Lowest temperature measured before ICU admission

^e^In surgical patients from anaesthesia induction until ICU admission; non-surgical patients: fluid balance (if available) upon ICU admission

^f^Hemoglobin, leucocytes, erythrocites, haematocrit, mean corpuscular volume (MCV), mean corpuscular haemoglobin (MCH), mean corpuscular haemoglobin concentration (MCHC), red cell distribution width (RDW), thrombocytes, quick, international normalised ratio (INR), activated partial thromboplastin time (APTT), thrombin time 1 (TZ1), fibrinogen and β-subunit of human chorionic gonadotropin (βHCG) in female study participants of reproductive age < 45 years

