### Other outcome measures

#### Platelet function analysis

Before the administration of the study drug and 30–60 min after administration of the study drug, platelet function analysis (VerifyNow® ADP test) will be performed to evaluate the possible improvement of platelet function by timely adding vWF to platelets.

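### Platelet reactivity (PRU) is tested by an unadjusted t-test on change scores, which costs precision, and the sections disagree on when both PRU samples are drawn

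*Protocol article*

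**What the plan says.** **Analysis.** Under Secondary analyses, Thrombocytes activity, the protocol article names a t-test that "evaluates the difference in the outcome between the two study groups". It continues: "The outcome is defined as the difference in the platelet reaction units (PRU) measured with the VerifyNow® ADP test before and after" the platelet transfusion. No baseline covariate is named.

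**First sample.** Four places give its timing:
- Laboratory parameters (under Safety outcome measures) describes the VerifyNow test as one "which will be analysed right before the first study-specific platelet transfusion and 30–60 min after administration of the study drug and platelets".
- Platelet function analysis (under Definitions/conditions) gives "Before the administration of the study drug and 30–60 min after administration of the study drug".
- Table 2 lists "Platelets function analysis (VerifyNow® ADP test) *before* administration of the study drug", with the key word emphasised.
- Table 1 marks the test in the screening column (-1 h) and the 30–60 min column, and not at time 0.

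**Gap between drug and platelets.** The drug comes first. Experimental intervention says that "a minimum waiting period of 10 min should be met" where possible, and calls 20–30 min ideal. Adherence to intervention protocols gives at least 5 min.

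**Second sample.** Table 3 and Platelet function analysis count 30–60 min from the study drug. Laboratory parameters counts it from the drug and the platelets.

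**Status.** Platelet function is listed under Other outcome measures, although its analysis stands under Secondary analyses.

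**The concern.** There are two separate issues.

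The first is precision. A change score subtracts the whole baseline value, whatever the correlation between the two measurements. ANCOVA estimates how much of the baseline to subtract, using data that are already collected. Baseline PRU is likely to vary: patients with and without single or dual antiplatelet drugs are eligible, and the assay is designed to detect the effect of such drugs. The article accepts the principle elsewhere. It adds covariates to the primary model for precision, and it adjusts the analyses of blood loss, mortality and length of stay.

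The second is what the baseline measures. Because the drug precedes the platelets, a sample drawn directly before the platelets can already carry some drug effect. Subtracting it removes part of what the comparison is meant to show. A baseline sample drawn too late cannot be recovered.

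**Working it through.** **Inputs.** The document gives no correlation, SD or expected effect for PRU, so there is no stated PRU figure to reproduce. The planned 120 patients (60 per arm) were set for the primary outcome; this point does not test that number. Assumed here: equal SD before and after (set to 1), correlation ρ from 0.3 to 0.9, a true effect of 0.5 SD, two-sided 5%, and all 60 patients per arm measured.

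**Step 1: precision.** For post minus b times baseline, the variance is 1 + b² − 2bρ.
- Change score (b = 1): 2(1 − ρ).
- ANCOVA (b = ρ, the minimum): 1 − ρ².
- Excess of the change score: 2(1 − ρ) − (1 − ρ²) = (1 − ρ)², never negative.
- Ratio of ANCOVA to change score: (1 + ρ)/2.

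Detectable difference at 80% power = (1.960 + 0.842) × SD of the analysed quantity × √(2/60).

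| ρ | Variance, change | Variance, ANCOVA | Ratio | Detectable difference in SD, change / ANCOVA | Power at 0.5 SD, change / ANCOVA |
|---|---|---|---|---|---|
| 0.3 | 1.40 | 0.91 | 0.65 | 0.605 / 0.488 | 63.9% / 81.9% |
| 0.5 | 1.00 | 0.75 | 0.75 | 0.511 / 0.443 | 78.2% / 88.5% |
| 0.7 | 0.60 | 0.51 | 0.85 | 0.396 / 0.365 | 94.2% / 97.0% |
| 0.9 | 0.20 | 0.19 | 0.95 | 0.229 / 0.223 | both about 100% |

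**Step 2: which texts conflict on the first sample.** Tables 1 and 2 and Platelet function analysis all place it before the drug. Laboratory parameters ties it closely to the platelet transfusion, which follows the drug by at least 5 or 10 min, ideally 20–30 min. That wording therefore allows a sample after the drug. Thrombocytes activity says only before the transfusion. A pre-drug sample also satisfies this, so that section is imprecise rather than contradictory.

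**Step 3: effect of a post-drug first sample.** Suppose a share f of the effect δ, in the same direction, is already present in the first sample. The change-score contrast becomes (1 − f)δ. The ANCOVA contrast becomes (1 − ρf)δ. The document does not give f, so these values only illustrate the mechanism at δ = 0.5 SD:

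| ρ | f | Contrast kept, change / ANCOVA | Power, change / ANCOVA |
|---|---|---|---|
| 0.5 | 0 | 1.00 / 1.00 | 78.2% / 88.5% |
| 0.5 | 0.25 | 0.75 / 0.875 | 53.7% / 79.0% |
| 0.5 | 0.50 | 0.50 / 0.75 | 27.7% / 66.0% |
| 0.7 | 0 | 1.00 / 1.00 | 94.2% / 97.0% |
| 0.7 | 0.25 | 0.75 / 0.825 | 75.5% / 88.6% |
| 0.7 | 0.50 | 0.50 / 0.65 | 42.4% / 70.3% |

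ANCOVA loses less, but it does not restore the contrast.

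**Step 4: second sample.** If the clock starts at the drug and the platelets start 5 to 30 min later, the sample falls between 30 − 30 = 0 and 60 − 5 = 55 min after the platelets start. If the clock starts once drug and platelets have both been given, the sample falls 30–60 min after the platelets. These are different measurements.

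**The case against.** The defence has real force, and it limits how far the point can be taken.

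- *A reader might infer that the planned baseline is post-drug.* The document does not support this. Three places put it before the drug, and Table 2 stresses the word. Only Laboratory parameters points the other way. What stands is a contradiction to be removed, not a settled post-drug baseline.
- *A reader might infer that the change score throws the baseline away, or that regression to the mean biases the comparison.* Neither holds. The change score uses the baseline with a fixed coefficient of 1. With a pre-drug baseline, randomisation makes regression to the mean equal in expectation across arms. The t-test is then valid, and chance imbalance costs only precision.
- *The precision gain depends on an unknown correlation.* True. Stable differences between patients, such as antiplatelet use, would tend to raise the correlation and shrink the gain to about 5% at ρ = 0.9. The intervening platelets could lower it. The gain cannot be negative in large samples.
- *Detail belongs to the statistical analysis plan.* The article does defer detail, but here it names the test and defines the outcome, so the choice has already been stated.
- *The outcome is minor.* It is an other outcome, and nothing here touches the primary analysis, the sample size or safety. This limits the weight of the point but does not remove it.

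**Conclusion.** The point holds in two limited parts.

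1. The unadjusted change-score t-test is valid with a pre-drug baseline but less precise than ANCOVA. The variance ratio is (1 + ρ)/2, or 65% to 95% for ρ from 0.3 to 0.9. This is equivalent to the same precision with 35% to 5% fewer patients. It assumes equal SDs before and after; ρ is not in the document.

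2. The timing text contradicts itself. Laboratory parameters allows a first sample after the drug, against Tables 1 and 2 and Platelet function analysis, and Thrombocytes activity does not settle the matter. If such samples are drawn, any early drug effect in the same direction is partly subtracted and the contrast moves toward zero. The document does not allow the size to be estimated, and a change of model would not cure it. The second sample has two incompatible anchors as well.

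The consequence is confined to a mechanistic outcome.

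**What to change.** - In Thrombocytes activity, replace the t-test by a linear model of post-treatment PRU on treatment arm and baseline PRU. Prior antiplatelet use, already collected in Table 2, may be added as a covariate.
- Reword Laboratory parameters and Thrombocytes activity so that baseline PRU is the sample taken before study drug or placebo, as in Tables 1 and 2 and Platelet function analysis.
- State one starting point for the 30–60 min sample and use it in Laboratory parameters, Platelet function analysis and Tables 1 and 3.
- Reconcile the 5-min and 10-min drug-to-platelet intervals in Adherence to intervention protocols and Experimental intervention. No view is taken here on which is right.

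The cost is one sentence on the model and a few wording alignments, with no new data. The article requires a protocol amendment for substantial deviations from the planned analysis, so the change is best made before the analysis plan is final. The sampling text should be corrected while patients are still being sampled.
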